## Discussion

The current project aims to enhance FCC in a level III NICU in Gießen, Germany. The FINE (Family Infant Neurodevelopmental Education) education in FCC has been introduced as baseline but FCC depends on repetitive evaluation, propagation of its aims and stepwise implementation of further focus fields. The study continuously assesses whether the implemented changes to advance FCC improve FCC indicators and multidimensional outcomes. Infant, parents and staff outcomes are evaluated separately and interactions between these three dimensions will be analyzed as well. To our best knowledge, this is the first study systematically assessing the further enhancement of FCC in such a comprehensive way. A particular strength is that all data will be recorded separately for mothers and fathers. Although fathers have become more involved in the care of their preterm children only few studies have focused on the visiting patterns, involvement and well-being of fathers [40–43]. This study will provide further insight and can help to better support fathers of preterm infants.

Data on measurable indicators showing an increase of parental participation in the care of their preterm infant as a result of FCC interventions is scarce [43]. The standardized assessment tool and the CO-PARTNER tool will thoroughly document parental participation in several areas (kangarooing, visit time, different caregiving activities like bottle feed/breastfeeding, diaper change…) through charts at the bedside to be able to assess whether FCC interventions have an impact on parental skills.

Several professional societies endorse FCC by policy statements [1]. Although these policy statements exist, the practical implementation is varying across different countries, but also within countries [4, 5]. Disseminating innovations in health care is challenging with a considerable gap between knowledge and practice. To make change happen it is not enough that evidence for an intervention is available. The more difficult part is to translate evidence into local clinical practice [44]. To facilitate positive change management, a multidisciplinary team including nurses and physicians was implemented in the first stage with the aim to complement the team with parents of former preterm infants. This team consists of staff members with a special interest or expertise in FCC and will lead the process of innovation adjusted to the local neonatology department [45]. A multidisciplinary focus group was chosen to guide the implementation as successful dissemination of innovations in health care that is best achieved if a clinical guideline or recommendation is not merely repeated, but reinvented by the team and adjusted to the local context [19, 44]. The EPICE (Effective Perinatal Intensive Care in Europe) study group has identified the following three crucial factors for making change in the NICU happen: Innovation ideas that come from the NICU team itself and not from outside, active participation of the unit staff in the development and implementation of the innovation or policy change and the presence of staff members with personal interest in making the change happen [45].

FCC has been described as a journey with different neonatal units at different stages [46]. We have started on this journey four years ago and want to move further along the way.

QI efforts in healthcare have demonstrated variable results, some reporting positive changes in patient outcomes, others reporting no changes [20, 47, 48]. One possible reason for this variability is that e.g. the PDSA cycle has not been implemented rigorously in many studies [17, 18]. If implemented well, the PDSA cycle has the potential to lead to sustained improvement in healthcare and enable stepwise assessments and timely intervention [20]. Therefore, it is reasonable to not discard the method as such, but diligently apply the method. We will thoroughly consider the five key elements of the PDSA cycle identified as crucial by Taylor and Knudsen [17, 18]. The reporting will be done according to the SQUIRE 2.0 publication guidelines to ensure completeness, precision and transparency [49].

Changing the culture of a unit and the attitudes of individuals is challenging [7] and it is a very sensitive process. Acknowledging this Quality Improvement (QI) project as such a sensitive process we will evaluate staff satisfaction regularly. The implementation of changes often leads to an initial decline in staff satisfaction, followed by a recovery [50]. The scheduled 6 monthly assessment of staff satisfaction will enable us to realize early whether after an expected initial decline staff satisfaction recovers again.

This study will provide important insight into the application of a QI method to advance FCC in a NICU regarding the success of the QI method in achieving a higher degree of FCC and regarding team satisfaction during this change process.

Moreover statistical process control methods will be used as a novel approach to prospectively analyse the data over time and to understand and address the performance of the QI project [39]. This technique enables clinicians to detect process changes and trends earlier with the help of graphical display [51]. This approach has been suggested as a beneficial tool in neonatology [39, 47, 52]. The Canadian Neonatal Network recently published the results of a quality improvement initiative after a period of 14 years of experience using this technique [38]. Naturally, clinical data has some variation over time that is independent of interventions. Process control charts help to distinguish between natural variation and variation due to specific interventions.

The COVID pandemic starting at the beginning of our study was a big challenge as access to hospitals was greatly restricted in Germany also for the parents of NICU patients. Our results might give further insight into the consequences of these restrictions for the infant, parents and staff.

There are as well limitations to our study. The study is a single centre study undertaken in one neonatology department in Germany. The context of the particular neonatology department involved and its patient demographics including the socioeconomic and cultural background will influence the results. Due to the single center design the number of patients is restricted and a recruitment period of 5.5 years is needed. Changes of e.g. nurse-patient ratios on the basis of modifications of the obligatory national guideline of the Joint National Committee of Germany or towards the provision of active support according to the national AWMF guideline recommendations for the care of preterm infants at the border of viability will have an impact on the study results. Possible demographic changes over the study duration will also affect results. Nevertheless, our study pioneers the comprehensive evaluation of infant, parental and staff outcomes and when implemented successfully, the studied comprehensive assessment tool can be used to monitor and guide FCC interventions within a local or multicentre context in any other NICU.

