**Methods:**

This prospective single centre longitudinal cohort study enrols preterm infants ≤ 32 + 0 weeks of gestation and/or birthweight ≤ 1500 g and their parents at the neonatal department of the Giessen University Hospital, Giessen, Germany. Following a baseline period, the rollout of additional FCC elements is executed following a stepwise 6-months approach that covers the NICU environment, staff training, parental education and psychosocial support for parents. Recruitment is scheduled over a 5.5. year period from October 2020 to March 2026. The primary outcome is corrected gestational age at discharge. Secondary infant outcomes include neonatal morbidities, growth, and psychomotor development up to 24 months. Parental outcome measures are directed towards parental skills and satisfaction, parent-infant-interaction and mental health. Staff issues are elaborated with particular focus on the item workplace satisfaction. Quality improvement steps are monitored using the Plan- Do- Study- Act cycle method and outcome measures cover the infant, the parents and the medical team. The parallel data collection enables to study the interrelation between these three important areas of research. Sample size calculation was based on the primary outcome.

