### Timeline

The current status (baseline data) will be assessed in a baseline cohort of 45 preterm infants and their parents, as this is the average number of patient admissions per 6 months fulfilling the inclusion but not meeting the exclusion criteria during the last 5 years. The following cohorts will consist of all included infants who are recruited consecutively within 6-month-periods and their parents. The duration of the study will be 5.5 years with the first interim analysis after 2 years of start of the first intervention phase. A study period of 5.5 years for recruitment was chosen because shorter time periods have been associated with lacking results [7].

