**Fig. 3 Fig3:**
[figure not shown]
Process control chart

Process control charts will be used to describe, visualize, detect and understand changes in processes of care and outcomes [39]. Crude rates or medians will be plotted using 6-month periods to provide sufficient time points for process control chart analysis while maintaining more than 40 observations for subgroups [39]. For each graph, upper and lower control limits will be determined using standard statistical process-control parameters (± 3 standard deviations) using 6 months baseline data. We aimed to have 21 data points. Special-cause variation in outcomes will be defined as (significant changes that are not part of random variation) as any data point beyond the control limits, or 6 sequential points on 1 side of the mean, in either direction [38].

Second, linear trends for changes in FCC care practices, patient characteristics, and outcomes will be analyzed using F or Wald χ2 tests from linear or logistic regression models with 6 months periods used as continuous variable. Models will be adjusted using a generalized estimating equation approach (to account for clustering) with symmetric covariance structure, for the common variables known to be associated with the outcomes: e.g. gestational age in weeks (as a categorical variable), sex, demographics, multiple births, small for gestational age, outborn status, Score for Neonatal Acute Physiology version II (SNAP II) greater than 20, antenatal steroids, and change in major medical interventions. Change in major medical interventions was included because there may be future changes such as general stem cell transplantation or artificial placenta, which may have a tremendous effect on the long term outcome.

Data management and statistical analyses will be done using Microsoft^R^ EXCEL and R version 3.2.2 A 2-sided p value of less than 0.05 will be regarded as statistically significant. Data imputation will be done by study nurses and students and cross checked by the GCP qualified investigators. Source data will remain within the study site.

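### The baseline cohort falls in the period of restricted parental access, and no named model term separates the easing of those restrictions from an effect of family centred care (FCC)

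*Protocol article*

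**What the plan says.** **Timing.** The Abstract states: "Recruitment is scheduled over a 5.5. year period from October 2020 to March 2026". It gives the order of phases as follows: "Following a baseline period, the rollout of additional FCC elements is executed following a stepwise 6-months approach". Under Timeline, "The current status (baseline data) will be assessed in a baseline cohort of 45 preterm infants and their parents", which is about six months of admissions. Every later cohort is recruited during the rollout, and there is no concurrent control.

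**Restrictions.** The Discussion places the pandemic at the start of the study and says that "access to hospitals was greatly restricted in Germany also for the parents of NICU patients". It then adds: "Our results might give further insight into the consequences of these restrictions for the infant, parents and staff". The limitations paragraph that follows names staffing ratios, viability guidelines and demographic change, but not the pandemic.

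**Analysis.** Statistical assessment sets chart limits by "standard statistical process-control parameters (± 3 standard deviations) using 6 months baseline data" and tests a linear trend with the six-month period as a continuous variable. The covariate list opens with e.g. and names gestational age, then "sex, demographics, multiple births, small for gestational age, outborn status", an illness severity score, antenatal steroids and change in major medical interventions. The last is justified by possible stem cell transplantation or an artificial placenta.

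**Mechanism.** The Background hypothesises that more active parental involvement shortens the hospital stay. Visit duration and kangaroo time are recorded as parental outcomes.

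**The concern.** Both inferential tools lean on the early periods: the charts take their limits from the baseline, and the trend test is a slope over calendar time. Restricted access acts on parental presence, which is the route by which FCC is supposed to work. If access eased while FCC was being rolled out, the two changes run in the same direction over the same calendar axis, and a slope in period picks up both.

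The plan makes room for hypothetical future technologies but names no term for a disturbance that it reports as having already happened. It also hopes to learn about the consequences of the restrictions, which would need a restriction variable.

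At stake is the attribution of a favourable trend in corrected gestational age (cGA) at discharge. The problem is most direct for visiting and kangaroo time, which access rules affect without any intermediate step.

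**Working it through.** **The plan's own figures.** The protocol gives no figure for this bias. Its sample size does reproduce: a one-way analysis of variance with 11 levels, alpha 5% and Cohen's f = 0.5 has power 95.65% at N = 110. The layout is also consistent: 5.5 years in six-month steps gives 11 periods, and 90 eligible infants a year gives 45 per period.

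**Inputs from the protocol**
- 11 equal periods (Abstract; Sample size calculation).
- At least 300 enrolled infants, about 27 per period (Sample size calculation).
- SD of cGA at discharge 4.0 weeks for all very low birthweight (VLBW) infants, or 2.1 weeks after five late discharges are left out (Background to the sample size).
- Two-sided 5% test (Statistical assessment).

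**Assumptions.** Restrictions raised mean cGA at discharge by d = 0.5 or 1 week during the first m = 1, 2 or 3 periods; the true FCC effect is zero. The protocol gives neither d nor m.

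**Step 1: spurious decline.** Code the periods t = −5, …, 5, so Sxx = Σt² = 110. The baseline alone carries 25/110 = 23% of Sxx. The fitted change over the ten steps is 10 × d × (sum of the first m values of t) / 110. For d = 1:
- m = 1: 10 × (−5)/110 = −0.45 weeks
- m = 2: 10 × (−9)/110 = −0.82 weeks
- m = 3: 10 × (−12)/110 = −1.09 weeks

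For d = 0.5 these halve.

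**Step 2: standard error of that change.** SE = 10 × SD / √(300/11 × 110) = 10 × SD / √3000. This is 0.383 for SD 2.1 and 0.730 for SD 4.0.

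**Step 3: chance of a significant trend.** With z = |change|/SE, P = Φ(z − 1.96) + Φ(−z − 1.96). For d = 1, m = 3 and SD 2.1, z = 1.09/0.383 = 2.85 and P = 0.81.

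| SD (weeks) | d (weeks) | m = 1 | m = 2 | m = 3 |
|---|---|---|---|---|
| 2.1 | 1 | 22% | 57% | 81% |
| 2.1 | 0.5 | 9% | 19% | 30% |
| 4.0 | 1 | 10% | 20% | 32% |
| 4.0 | 0.5 | 6% | 9% | 12% |

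With 45 infants per period, and allowing for lack of fit to a straight line, the same d with m = 1 to 3 gives about 12–95% (SD 2.1) and 7–48% (SD 4.0).

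**Step 4: charts.** The rules (a point beyond the limits, or six in a row on one side) were simulated 20,000 times for period means with limits at ±3 standard errors, 45 infants per period and SD 2.1, with the single baseline mean as centre line. A favourable signal appeared in about 24% of runs with no shift. With m = 3 it appeared in about 73% for d = 0.5 and 98% for d = 1. The no-shift rate is already high because one baseline point fixes the centre. The plan charts medians or crude rates, so these figures are only indicative.

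**The case against.** **The list is open.** It begins with e.g., so a restriction term is not ruled out, and a full analysis plan may contain one. That stands: the fair statement is that the term is not named. It does not settle the matter, because the article goes as far as justifying one time-varying term and confines the explanation to medical technology.

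**The restrictions are disclosed.** A reader might infer that their easing will be reported as an FCC effect. The protocol does not say so. It acknowledges the restrictions and says that improvements cannot be allocated to individual FCC steps. What can be said is that the described analysis cannot tell the two apart.

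**Timing and direction are inferred.** The protocol gives no dates, no account of access rules in this unit and no effect on discharge age. The favourable direction rests on the investigators' own untested hypothesis. This limits confidence for the primary outcome more than for visiting and kangaroo time.

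**The larger percentages need favourable inputs.** One week is half of the two-week target. SD 2.1 leaves out five late discharges, whereas the exclusion criteria do not remove such infants. This stands, and it is why the whole table is shown, down to 6%. Adjustment for gestational age would lower the residual SD by an amount that the protocol does not give.

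**Staffing ratios.** The nurse-patient ratio is a separate limitation that the protocol already discloses; no direction or size can be given for it here.

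**Conclusion.** The concern holds as a problem of identification. The single baseline lies where the protocol itself puts greatly restricted parental access, it anchors both the charts and the trend, and no named covariate represents the restrictions. A favourable trend would therefore have a rival explanation that the described analysis cannot exclude.

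The size is unknown. Under the stated assumptions the false-positive rate runs from close to nominal (6%) to 81% with 300 infants, depending on the shift, its duration and the SD. The conclusion needs only that access eased during the study and that it matters for the outcome. The stronger readings, that the plan excludes adjustment or that the bias is known to be large, are not supported.

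**What to change.** 1. **Add a restriction variable to the adjusted models, defined by calendar date.** Suitable forms are restriction status at birth or the share of a fixed window after birth; for staff outcomes, the share of the six-month period. It should not be the share of the infant's own stay: that share depends on length of stay, which is what the primary outcome measures, so adjusting for it would bring in a new bias.
2. **Pre-specify a sensitivity trend without the restricted periods.** Redraw the charts with limits from unrestricted periods or from eligibility-matched pre-pandemic records. The 2018–19 figures describe VLBW infants, whereas the trial also admits infants on gestational age alone, so they may serve only after matching to the inclusion criteria.
3. **State the limit on attribution.** If only the baseline period was restricted, the variable coincides with baseline and cannot separate the two. The sensitivity trend then describes change within the rollout only. In that case a baseline-versus-later difference should not be attributed to FCC.

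The nurse-patient ratio may be added as a period-level covariate.

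**Cost.** The restriction dates have to be documented, and the interval widens because restriction correlates with calendar time. For the sensitivity trend with equal numbers per period, dropping one period takes Sxx from 110 to 82.5, so the SE of the slope rises by √(110/82.5) − 1 = 15%. Dropping three takes it to 42, a rise of √(110/42) − 1 = 62%. Recruitment and care do not change.

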## Data Availability

Not applicable.

## Abbreviations

FCC: Family Centered Care
NICU: Neonatal Intensive Care Unit
PDSA: Plan- Do- Study- Act
FiCare: Family Integrated Care
NIDCAP: Newborn Individualized Developmental Care and Assessment Program
GA: Gestational Age
GCP: Good Clinical Practice
FINE: Family Infant Neurodevelopmental Education
PBP: Potentially Better Practices
DOL: Day of Life
CPAP: Continuous Positive Airway Pressure
HFNC: Highflow Nasal Cannula
NES: Neuropsychologische Entwicklungsscreening
GMFCS: Gross Motor Function Classification System
HADS-D: Hospital and Anxiety and Depression
PSI: Parenting Stress Index
EBI: Eltern-Belastungs-Inventar, EBI
COPSOQ: Copenhagen Psychosocial Questionnaire
cGA: Corrected gestational age
EPICE: Effective Perinatal intensive Care in Europe
QI: Quality Improvement
FINE: Family Infant Neurodevelopmental Education
NEC: Necrotizing enterocolitis
ROP: Retinopathy of prematurity
